##### Quantitative analysis of bundle compliance

Bundle compliance will be defined as all-or-nothing for the individual elements of the bundles. The statistical analysis will be similar to the primary analysis for hospital mortality.

##### Qualitative analyses of bundle compliance

We will supplement quantitative analyses with qualitative interviews with key informants (ED leaders, physicians, and nurses) during the Exploration and Sustainment Phases and qualitative process evaluation data from the Implementation Phase learning collaborative meetings. For the Exploration and Sustainment Phases, we will recruit participants until thematic saturation is reached [69], anticipating up to 5 participants per site during each Phase (*N* = 90). For the Implementation Phase, learning collaborative meetings will be recorded and coded as process evaluations by the study team. Learning collaborative meetings will be recorded but will not be transcribed; instead, detailed notes will be taken during interviews and collaborative meetings. Qualitative interviews will be coded using a rapid analytic approach described by Hamilton [70], in which a template is developed to summarize transcripts. The deductive domains for this summary template will be based on the interview guides with additional space for other observations and reflections. The qualitative team will also be able to add inductive domains to the template in response to the data collected [71]. The data entered into the summary template will be analyzed using matrix analysis [72].

#### Aim 3: Identify four discrete, previously validated, sepsis phenotypes, two of which may identify patients who are significantly more likely to benefit from the 1-h bundle (γ and ∂)

Recently, the Sepsis ENdotyping in Emergency CAre (SENECA) project derived and evaluated sepsis phenotypes using clinical data from presentation in the ED. Using a variety of unsupervised clustering methods, 4 sepsis phenotypes (*α*, *ß*, *y*, and ∂) were derived, using 29 clinical variables such as vital signs, laboratory values, and demographics [73]. These phenotypes were validated in 6 studies across > 60,000 patients and found to have differences in clinical features, host response biomarkers, and clinical outcomes. In the present study, routine clinical variables will be extracted through EHR data or manual entry within the first 24 h of sepsis onset. Sepsis phenotypes will be determined using multivariate modeling. To understand if treatment effectiveness of the 1-h bundle are differentiated by phenotype, we will use unadjusted random-effects logistic regression with the following risk factors: phenotype, intervention arm, and the interaction of these two variables.

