### Study objectives

The study aims are as follows: (*Aim 1*) Examine comparative effectiveness of the 1-h versus 3-h sepsis bundle on the primary outcome of hospital mortality and secondary outcomes of length of stay, ventilator-free days at 28 days, and rate of acute respiratory failure requiring mechanical ventilation. *Hypothesis:* The 1-h bundle will have lower hospital mortality. (*Aim 2*): Conduct a mixed methods evaluation of a multi-faceted implementation strategy to enhance compliance with the 1 and the 3-h bundles. *Hypothesis*: 1 and 3-h bundle implementation compliance will be similar as assessed by (a) the electronic health record (EHR), (b) surveys of key informants regarding implementation climate, organizational readiness for change, and implementation leadership, (c) recordings of learning collaborative meetings, and (d) interviews with participants. (*Aim 3*): Determine if clinical sepsis phenotypes determined by characteristics measured at presentation modify the treatment effect of the 1 or 3-h bundle. *Hypothesis:* Routine clinical information available at ED presentation will identify phenotypes more likely to benefit from the 1 or 3-h bundle.

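### Aim 3 promises phenotypes measured at presentation, but the analysis plan takes their inputs from a 24-h window that contains both bundles, so phenotype can be affected by the assigned arm

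*Protocol article*

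**What the plan says.** The protocol article gives two measurement times for the Aim 3 phenotypes.

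- *Study objectives*, the aim: "Determine if clinical sepsis phenotypes determined by characteristics measured at presentation modify the treatment effect of the 1 or 3-h bundle". The hypothesis says the same: "Routine clinical information available at ED presentation will identify phenotypes more likely to benefit from the 1 or 3-h bundle".
- *Analysis plan, Aim 3*: the source project "derived and evaluated sepsis phenotypes using clinical data from presentation in the ED", "using 29 clinical variables such as vital signs, laboratory values, and demographics". For this trial, however, "routine clinical variables will be extracted through EHR data or manual entry within the first 24 h of sepsis onset".

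The Aim 3 model is an unadjusted random-effects logistic regression whose terms are "phenotype, intervention arm, and the interaction of these two variables". The section does not say whether it is fitted to the outcome phase alone or to the baseline and outcome periods together.

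**The concern.** A test of effect modification needs a modifier that the assigned treatment cannot have changed. Antibiotics, fluids and vasopressors are meant to alter blood pressure, lactate and other vital signs and laboratory values, and the phenotype inputs include variables of that kind. If values recorded after the bundle has started enter the classification, patients with the same phenotype label in the two arms are no longer comparable, and the comparison within a phenotype loses the protection of randomisation. A benefit in a sicker phenotype could be hidden, or a harm could appear, only because earlier treatment moved patients between classes.

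There is also a practical point. The Discussion expects phenotypes to identify patients who benefit from an appropriately timed bundle. A classification that is complete only at 24 h is not available when the choice between 1 h and 3 h is made.

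**Working it through.** **1. The timings side by side**

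| Item | Time | Source in the protocol article |
|---|---|---|
| Phenotype inputs as promised | ED presentation | Study objectives, Aim 3 |
| Inputs used to derive the cited phenotypes | ED presentation | Analysis plan, Aim 3 |
| Phenotype inputs in this trial | up to 24 h after sepsis onset | Analysis plan, Aim 3 |
| Bundle elements, 1-h arm | within 1 h of time zero | Compliance definition |
| Bundle elements, 3-h arm | within 3 h of time zero | Compliance definition |

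The article does not define sepsis onset relative to time zero. If they coincide, the bundle windows end at 1 h and 3 h, inside 24 h. The Study setting section requires the three criteria to be met within 6 h. If onset means the first criterion met, the 3-h window still ends by 6 + 3 = 9 h. On either reading, both bundle windows lie inside the extraction window.

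**2. How much this could matter: a simulation on assumed inputs**

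The article gives no sample size, power or effect size for Aim 3, so there is no figure to reproduce. The model used 4 million patients per arm:

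- Severity S is standard normal, and logit(mortality) = a + 1.2·S + ln(0.903)·arm. The constant a gives 20.3% mortality in the 3-h arm (Table 4). The OR of 0.903 is 18.7% against 20.3% (Table 4). There is no true interaction.
- A patient is classed as severe if S plus noise (SD 0.5) exceeds 0.5.
- In the window version, the measured score in the 1-h arm is lowered by a fixed shift.

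The slope, noise, cut-off and shifts are assumptions.

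| Phenotype measured | Arm OR, severe | Arm OR, other | Interaction ratio | Severe class in 1-h arm |
|---|---|---|---|---|
| At presentation | 0.91 | 0.91 | 1.00 | 33% |
| In window, shift 0.1 SD | 0.97 | 0.96 | 1.01 | 30% |
| In window, shift 0.2 SD | 1.03 | 1.01 | 1.02 | 27% |
| In window, shift 0.4 SD | 1.18 | 1.12 | 1.06 | 21% |

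If only patients with above-average severity are shifted, the interaction ratio moves the other way: 0.99, 0.98 and 0.98 for the same three shifts. The class-specific ORs still rise, to 1.09 and 1.12 at 0.4 SD.

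**3. A hand check by class migration, also on assumed inputs**

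Take a phenotype with 15% prevalence and 40% mortality, 15% mortality elsewhere, and no effect of timing. Let a fraction f of the phenotype, with 25% mortality, move out under 1-h care.

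- Mortality left in the phenotype: (0.40 − 0.25f)/(1 − f)
- Mortality in the rest: (0.85·0.15 + 0.15·f·0.25)/(0.85 + 0.15f)

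For f = 0.10 these are 0.375/0.90 = 41.67% and 0.13125/0.865 = 15.17%. The shifts are 1.67 and 0.17 points, a spurious interaction of 1.49 points. For f = 0.05 and 0.20 it is 0.70 and 3.41 points. On the logistic scale that the plan uses, the three interaction odds ratios are about 1.03, 1.06 and 1.14.

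**4. The period term, if both periods are pooled**

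Table 4 reproduces: 0.80·18.9 + 0.20·26.1 = 20.34, and 0.70·16.2 + 0.30·24.4 = 18.66. Pre-intervention mortality is 23.2% in both arms.

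- Outcome phase only: OR = (0.187/0.813)/(0.203/0.797) = 0.903, a difference of 1.6 points.
- Pooled with equal numbers per period: (23.2 + 18.7)/2 = 20.95% and (23.2 + 20.3)/2 = 21.75%. OR = (0.2095/0.7905)/(0.2175/0.7825) = 0.953, a difference of 0.8 points.
- Ratio of log ORs: ln(0.953)/ln(0.903) = 0.47 (unrounded ORs).

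**The case against.** The strongest reply is that 24 h is an extraction window and not a rule for choosing a value. If it only limits the search for the first available value, most inputs could precede the bundle and agree with the Study objectives, and the value-selection rule is a detail that a fuller document may hold. This stands against any claim that bias is certain. It does not remove the conflict: the article states two measurement times, and nothing in it ties the second back to the first.

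A reader might infer three stronger conclusions that the documents do not support.

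- *That the effect-modification analysis will be biased.* Bias arises only if post-treatment values are used and bundle timing moves them.
- *That a false interaction would be as large as the trial's target effect.* The 0.70 to 3.41 points rest on invented inputs and correspond to odds ratios of only about 1.03 to 1.14. They show spurious harm only, since mortality rises in both classes. The 1.6 and 2.7 points in the power section are main-effect figures; the article sets no target for Aim 3.
- *That the model is wrong for want of a period term.* The Sustainment phase section calls the outcome-phase data the primary data set, to be compared with baseline. On outcome-phase patients alone, the listed model is coherent as a post-intervention comparison.

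It is also fair to say that Aim 3 is a secondary aim, presented as exploring heterogeneity, and that the primary analysis is untouched.

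**Conclusion.** The point holds as a contradiction that should be corrected. The stated 24-h window conflicts with the aim and admits values that the assigned bundle may already have changed. The textual conflict is certain; the bias is possible, and its size is unknown.

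On the assumed inputs, the phenotype-specific arm effects are the more vulnerable quantity: they can move from about 0.91 to above 1. The interaction ratio is distorted less, and its sign depends on which patients shift. Even without bias, a class that needs 24 h of data does not serve the stated purpose.

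The period point is secondary and applies only if baseline and outcome data are pooled. With Table 4 figures and equal numbers per period, the arm effect then falls to about 47% of its log OR.

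**What to change.** 1. State that phenotype inputs are values recorded at or before time zero, or the first ED value recorded before any bundle element, in line with the Study objectives. Keep the 24-h classification, if wanted, as a sensitivity analysis labelled as using post-randomisation data.
2. Name the period for Aim 3. Either fit the listed model to outcome-phase patients only, or add period and its interactions and make phenotype × arm × period the test.

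The text changes are one extraction rule and one sentence on the model. The real costs lie in the data. More inputs will be missing at presentation, and the single general sentence on multiple imputation in the power section does not show that this is covered. Baseline collection began on December 1, 2022, and some variables may be entered by hand. If those entries carry no time stamp, which the article does not say, some re-abstraction may be needed. For baseline patients that would matter only if they enter the Aim 3 model.

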### Recruitment and power

The study sample size will (4070 in each arm) provide adequate power to detect a difference-in-difference in hospital mortality between the pre-intervention period and the post-intervention period. This estimate is based upon the number of patients who receive care compliant with the respective bundles and associated hospital mortality. Analyzing ED patients included in the New York Sepsis Database, pre-intervention hospital mortality was 19.1% for those compliant with the 3-h bundle. Analyzing the data to create cohorts compliant with therapies at 1 h and at 3 h, the post-intervention hospital mortality of those receiving care compliant with the 1-h bundle was 16.2% and hospital mortality for those receiving care compliant with the 3-h bundle was 18.9% (preliminary data submitted to NHLBI R01 HL153268). This is based on the assumption that in the post-intervention period, the median time to antibiotics will be reduced by a quarter of an hour (25% reduction) in the 1-h arm. This quarter of an hour reduction in time to antibiotics translates to a 0.2% reduction in hospital mortality. Table 3 summarizes the assumptions used in the power calculation.

**Table 3 Tab3:** Assumptions for Donner and Klar’s cluster-randomized power calculation using a mixed model test for two proportions in a 2-level hierarchical design. An intraclass correlation coefficient of 0.025 is based on ED patients in the New York Sepsis Clinical Database

Compliant ED patients with the bundle	Pre-intervention mortality, %	Intervention period	Post-intervention mortality, %	Difference	Difference in difference
3-h arm	19.1		18.9	0.2%	2.7%
1-h arm	19.1		16.2	2.9%	

Using the power estimate methods of Donner and Klar, nine hospitals per arm with a minimum of 105 patients in each hospital will give 80% power to detect a 2.7% difference-in-difference in mortality, with *α* = 0.05, ICC = 0.025, and an equal number of hospitals per arm. To account for limitations in preliminary data, we increased the target number of patients by 50% to 158 patients. Since we expect bundle compliance in the 1-h arm to be 70%, 230 *total subjects* per hospital are needed. Table 4 shows the expected overall hospital mortality in the intent-to-treat analysis based on these assumptions. Multiple imputation will be used to handle missing data.

**Table 4 Tab4:** Estimated pre- and post-intervention overall mortality used in the intent-to-treat analysis

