### Analysis plan

#### Aim 1: 1-h bundle will have significantly lower patient mortality and improve all secondary outcomes

##### Primary outcome analysis

An intention to treat analysis of patient mortality in each arm will be evaluated in 2 ways: (1) the difference, in primary outcomes (hospital mortality), between the two arms during the 6-month baseline assessment and the 6-month outcomes assessment, and (2) the comparison between the first two differences (i.e., difference-in-difference estimation). This difference-in-difference analysis will be the *primary analysis* to assess the *primary hypothesis* of Aim 1: the 1-h bundle will result in lower mortality than the 3-h bundle. Both absolute and risk-adjusted hospital mortality will be reported. Random-effects logistic regression will evaluate all the mortality differences. The random term will be the hospital. This model will contain three binary risk factors: (1) 1-h arm vs. 3-h arm, (2) 6-month baseline period prior to randomization vs. 6-month outcome assessment phase, and (3) the interaction of these two terms. The effect of the intervention and the effect of the two time periods will be quantified by odds ratios while the differences in hospital mortality will be quantified by model probabilities. Additionally, the model will be adjusted for hospital level 3-h bundle compliance prior to intervention along with patient and hospital characteristics.

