## Discussion

This study represents a critical step in assessing sepsis bundle effectiveness and implementation strategies to support compliance. It will be the first rigorous cluster-randomized design used to evaluate sepsis bundles and will compare two different bundle timelines for accomplishing early metrics. In addition, a tailored implementation strategy to enhance the implementation of sepsis bundles represents a novel approach. Rigorous formative, process, and summative evaluations using a concurrent mixed methods approach will provide important information to sites to correct site-level implementation strategy problems. In addition to our pragmatic and hybrid effectiveness-implementation aims, we will also explore heterogeneity of treatment effects in recently described clinical phenotypes. These phenotypes may respond differently to the interventions, informing future studies of bundle effectiveness.

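### Aim 3 fixes the phenotype-by-arm model as unadjusted: valid, but it gives up some power in a weak interaction test and departs from the adjusted primary model

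*Protocol article*

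**What the plan says.** The Aim 3 section of the Protocol article's analysis plan sets the model out in full: "we will use unadjusted random-effects logistic regression with the following risk factors: phenotype, intervention arm, and the interaction of these two variables". This is a stated choice, not a detail left open. The phenotypes come from an earlier derivation "using 29 clinical variables such as vital signs, laboratory values, and demographics", and there are four of them.

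Under Primary outcome analysis, the Aim 1 model has arm, period and their interaction, with hospital as the random term. The article then adds that "the model will be adjusted for hospital level 3-h bundle compliance prior to intervention along with patient and hospital characteristics". The secondary-outcome and bundle-compliance analyses are said to follow the primary approach. Aim 3 is the only one of these model-based analyses that is fixed as unadjusted, and no reason is given. The Randomization section says allocation controlled for academic or community status, and the Aim 3 model omits that factor too.

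No power is stated for the Aim 3 interaction. The Discussion presents the aim as exploratory: "we will also explore heterogeneity of treatment effects in recently described clinical phenotypes".

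**The concern.** A test of whether the arm effect differs across four phenotypes is much weaker than a test of the overall arm effect. In a logistic model, leaving out strong prognostic covariates pulls the estimated odds ratios towards 1 and so costs power. Phenotype does not replace the covariates entirely. It reduces 29 variables to four classes, leaves risk varying within each class, and carries no hospital characteristics.

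With nine hospitals per arm, chance differences between the arms are likely. The phenotype-specific arm effects, which readers will look at first, would then rest on phenotype and the random intercept alone. At stake is some chance of seeing a real difference between phenotypes, and consistency with the way the rest of the trial is analysed.

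**Working it through.** **The plan's own figure.** None exists for Aim 3. The only power statement concerns the primary comparison: "nine hospitals per arm with a minimum of 105 patients in each hospital will give 80% power to detect a 2.7% difference-in-difference in mortality", with "ICC = 0.025, and an equal number of hospitals per arm". A simple post-period calculation does not reproduce it. The design effect is 1 + (105 − 1) × 0.025 = 3.6, so the effective number per arm is 945 / 3.6 = 262.5. Power for 18.9% against 16.2% is then 12.6% two-sided. That formula gives no credit for the baseline period. The discrepancy is a separate matter, and nothing below depends on it.

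**Inputs from the article.** There are 18 hospitals, 230 patients per hospital, an ICC of 0.025, and four phenotypes (so 4 − 1 = 3 degrees of freedom). Two of the phenotypes are expected to benefit.

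**Assumptions not in the article.**
- Phenotype shares are equal.
- 3-h arm mortality by phenotype is about 8, 15, 22 and 40%. The mean is (8 + 15 + 22 + 40) / 4 = 21.25%, near the 20.3% that Table 4 gives for that arm after the intervention.
- There is one prognostic covariate, independent of phenotype, with log-odds ratio per SD of 0.5 (modest), 1.0 (strong) or 1.5 (very strong).
- There is no arm effect in two phenotypes and a conditional odds ratio of 0.8, 0.67 or 0.6 in the other two.

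**Method.** Trials were simulated, the logistic model was fitted with and without the covariate, and the three interaction terms were tested jointly with a Wald test at 5%. Hospital intercepts were fitted as fixed effects.

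**Power, unadjusted → adjusted (gain in points).**

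| Odds ratio in two phenotypes | Modest covariate | Strong | Very strong |
|---|---|---|---|
| 0.8 | 16.5 → 18.2% (1.7) | 13.9 → 17.6% (3.7) | 11.8 → 15.4% (3.6) |
| 0.67 | 41.8 → 44.1% (2.3) | 36.4 → 42.7% (6.3) | 26.5 → 37.8% (11.3) |
| 0.6 | 63.9 → 67.5% (3.6) | 56.0 → 65.8% (9.8) | 45.0 → 58.8% (13.8) |

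With no interaction, the rejection rate was 4.4% to 6.0% across both models, so neither is invalid.

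**Where the gain comes from.** Take the odds ratio of 0.67, whose true log is −0.40, and divide the mean estimate by the mean standard error for one interaction term:
- Modest: 0.375 / 0.266 = 1.41 unadjusted; 0.395 / 0.270 = 1.46 adjusted.
- Strong: 0.338 / 0.266 = 1.27 unadjusted; 0.398 / 0.281 = 1.42 adjusted.
- Very strong: 0.290 / 0.266 = 1.09 unadjusted; 0.407 / 0.299 = 1.36 adjusted.

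The standard error rises with adjustment. The ratio improves because the estimate recovers the conditional effect.

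**A second run with other assumptions.** With an interaction of −0.5 on the log-odds scale in two phenotypes and a within-phenotype risk score of SD 0.6, 0.8 or 1.0, power went from 54 to 55%, 55 to 59% and 46 to 56%. There were 400 trials per setting, so each power has a simulation standard error of about √(0.54 × 0.46 / 400) = 2.5 points. The first of these gains is negligible.

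**The case against.** The strongest defence is that the arm is randomized, the aim is exploratory, and an unadjusted interaction test keeps its error rate. That stands: nothing here is an error. Because the phenotypes are built from vital signs, laboratory values and demographics, patient covariates overlap with them, and the modest column of the table may be the realistic one. That stands as well.

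Several stronger readings are tempting, and the documents do not support them.
- *A reader might infer that adjustment would sharpen the estimates.* In a logistic model it does the reverse to the standard error, as shown above.
- *A reader might infer that hospital case mix distorts the interaction test.* That contrast is mostly within hospital, so hospital covariates add little beyond the random intercept. The simulation cannot speak to hospital-level imbalance, because fixed hospital effects absorb it. Chance imbalance bears on the phenotype-specific arm effects, and its size was not estimated.
- *A reader might infer that Aims 1 and 3 analyse the same patients.* The primary model compares "6-month baseline period prior to randomization vs. 6-month outcome assessment phase". The Aim 3 model has no period term, and its section does not say which period's patients enter.
- *A reader might infer that adjustment would align the two aims' odds ratios.* Aim 1 targets arm by period and Aim 3 targets phenotype by arm. These remain different quantities.

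The missing period term is arguably the more consequential gap in the same sentence. If both periods were pooled, the interaction estimate was roughly halved in simulation (−0.185 against −0.386 with the three-way term, modest covariate), and adjustment did not repair it. It needs its own clarification.

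Finally, adding covariates without restriction could do harm. Aim 3 draws clinical variables from the first 24 h of sepsis onset, beyond both bundle windows, so some values could already reflect treatment.

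**Conclusion.** The point holds as a modest matter of efficiency and consistency. The unadjusted model is valid. It gives up about 2 to 4 points of power if covariates add modestly beyond phenotype, 4 to 10 points if they are strongly prognostic, and 4 to 14 points if very strongly so. Power was below 80% in every scenario tried, at 12 to 64% unadjusted and 15 to 68% adjusted, so adjustment does not make the test strong. These figures rest on the assumed covariate strength, phenotype shares, mortality and effect sizes. Lack of adjustment for chance imbalance between nine hospitals per arm is a reasonable concern for the phenotype-specific arm effects, but it has not been quantified.

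**What to change.** In the Aim 3 section, make the main model adjust for:
- academic or community status;
- baseline hospital 3-h bundle compliance;
- those primary-model patient covariates that are measured at or before time zero, excluding values from the 24-h window that treatment could affect.

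Keep the phenotype-by-arm interaction as the test and report the unadjusted result beside it.

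The cost is small: a short change of wording and no data beyond the primary model's covariates. The article does not name the patient covariates, so the list has to be fixed in advance and checked for timing. The two hospital-level terms reduce the between-hospital degrees of freedom from 18 − 2 = 16 to 14. Overlap between covariates and phenotype makes the phenotype main effect harder to read.
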